### Control

After randomization and allocating participants to 2 groups, those in the control group will receive the usual care. In HF clinic at THC, usual care for patients with HF is limited to a brief instruction by HF specialists on limiting water and salt intake, taking medications as prescribed, physical activity, weight monitoring and increasing the diuretic dosage in the condition of peripheral edema, weight gain, and SOB. They will receive 1 monthly phone call for 3 months. Out of respect for the ethical principles of human research, HF self-care instruction will be provided to the participants in the control group, and they will receive an educational booklet at the end of the study.

**Figure 1 figure1:**
[figure not shown]
Colored weight daily diary. EMS: emergency medical services.

**Figure 2 figure2:**
[figure not shown]
Colored shortness of breath daily diary. EMS: emergency medical services.

**Figure 3 figure3:**
[figure not shown]
Flowchart of actions recommended by research nurse based on color zones of each subject's self-monitoring daily diary during call follow-ups. ED: emergency department; EMS: emergency medical services; SOB: shortness of breath.

**Figure 4 figure4:**
[figure not shown]
Flowchart of the research nurse recommendations for each symptom reported by subjects in the intervention group during the call follow-ups.

### Study Measures

#### Primary Outcome

##### Self-Care Behavior

Effective self-care improvement is a priority of all clinicians caring for patients with HF [46]. In a developing country like Iran, there is a growing need to improve patient’s self-care [15]. However, there is a low rate of reported admissions for HF in Iran [3]. Thus, in contrast to previous studies where hospitalization was considered the primary outcome [21,22,30] and self-care as the secondary outcome [21,22], self-care has been identified as the primary outcome in this trial.

Self-care behavior will be measured by the Self-Care of Heart Failure Index (SCHFI) version 6.2 [47] by self-reporting at baseline and monthly intervals for 3 months. SCHFI was translated into Persian and validated for Persian speaking people by Siabani et al in 2014 [48]. It consists of 3 separate scales and 22 questions: 10 for self-care maintenance, 6 for self-care management, and 6 for self-care confidence [49]. Cronbach alpha was determined for self-care maintenance (.56), management (.64), and confidence scales (.79) [48]. Scale scores can range between 0 to 100, and a score ≥70 will be considered as adequate self-care [49]. We will ask participants to complete SCHFI by themselves at baseline and then monthly for 3 months.

#### Secondary Outcomes

##### Heart Failure Knowledge

In order to assess the effect of education and counseling on knowledge of participants with HF, the Dutch Heart Failure Knowledge Scale (DHFKS), with Cronbach alpha=.62, will be used. This scale consists of a 15 multiple-choice self- administered questionnaire concerning: general knowledge on HF (4 questions), knowledge on HF treatment (6 questions on diet, fluid restriction, and activity), and symptoms and their recognition (5 questions). The participants will be asked to choose the correct option from the three choices. The minimum score for this scale can range from 0 (no knowledge) to a maximum score of 15 (excellent knowledge) [50].

While there is no Iranian version of this scale, it was translated into the Persian language by forward-backward translation methods after obtaining permission from the scale developer [50]. The face and content validity were evaluated by an expert’s opinion and discussion with patients with HF. The reliability was assessed through a pilot study among 30 patients with HF (Cronbach alpha=.62). This coefficient alpha was identical to the original one, and the internal consistency could not be improved by deleting any of the 15 items [50]. Thus, all items have been retained. Participants will be asked to provide answers to the DHFKS by themselves at baseline and the end of the study.

##### Quality of Life

Heart failure quality of Life (HFQOL) will be assessed by the Iranian version of the Minnesota Living with Heart Failure Questionnaire (MLHFQ) with Cronbach alpha=.95 [51]. The psychometric properties of the questionnaire were evaluated by Middel et al in 2001 (Cronbach alpha≥.80 for the scales) [52]. The MLHFQ consists of 21 questions with a 6-point Likert scale ranging from 0 (without limitation) to 5 (maximum limitation). It consists of physical and emotional dimensions. The physical dimension is the sum of the question scores (questions 1 to 7, 12, 13) while the emotional dimension is based on questions 17 to 21. Questions 8 to 11 and 14 to 16 are related to lifestyle, financial situations, and side effects of medications. The total is the sum of the 21-question score, and a lower score reflects better quality of life [53]. Since this instrument assesses HFQOL in the previous month [54], we will ask participants to complete MLHFQ by themselves at baseline and then monthly for 3 months.

##### All-Cause Hospitalization

Data related to all-cause hospitalization during the previous month (ie, cause, date of admission, discharge, and length of stay) will be obtained from participants in both groups by an outcome assessor blinded to study group assignment during monthly call follow-ups. In the case of admission to other health care settings except for THC, data will be collected according to the participants’ self-reporting. If the participant is admitted to THC, data will be confirmed by the hospital information system following participant self-reporting.

Causes of hospital admissions will be classified according to 3 categories of cardiac admission for HF: SOB and edema relieved by diuretics, other cardiac causes (ie, chest pain, arrhythmias, or syncope), and non-cardiac causes [21]. All-cause hospital admissions will be obtained by trained research assistants who are blinded to the allocation.

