## Introduction

Heart failure (HF) is a complex clinical syndrome that results from any structural and functional impairment of ventricular filling or ejection of blood. Based on left ventricle dysfunction and the left ventricle ejection fraction (LVEF), HF can be categorized as preserved ejection fraction (with LVEF≥50%, known as HFpEF or diastolic HF) and reduced ejection fraction (with LVEF ≤40%, known as HFrEF or systolic HF) [1].

As a global burden, HF affects more than 37.7 million individuals worldwide [2] and is a common condition with 1%-2% total health resources allocated in high-income countries. In low- and middle-income countries (LMICs) like Iran, HF may displace infectious diseases as the major public health issue [3]. In Iran and other Asian LMICs, HF is described as a pandemic [4], the prevalence greatly increased with age and range between 0.5% to 9.0% among different cities, regardless of time distribution [5], thus supporting the need for better HF surveillance and management strategies [3]. Patients with HF can experience various clinical outcomes including mortality, morbidity, and other patient-reported outcomes [6]. Although mortality and morbidity rates are similar for HFpEF and HFrEF, the hospital admission rates in patients with HFrEF are much higher than HFpEF [7].

HF is a leading cause of hospitalizations [8], mortality [8,9], rising health care costs (over US $39 billion annually in the United States and US $53.1 billion by 2030) [2,8-10], suboptimal self-care behavior [11], and reduced quality of life (QOL) [12]. According to a recent European Society of Cardiology Heart Failure Long-Term Registry prospective observational study, the rate of all-cause mortality and hospitalization at one-year follow-up was 8.1% and 28.2%, respectively [13]. Compared to Western countries, patients with HF in Asia and Iran are younger, have more severe signs and symptoms, and receive lower levels of treatment compared to the European Society of Cardiology and American College of Cardiology Foundation/American Heart Association Guidelines [14]. Moreover, Callender et al [3] reported that Iranian patients with HF experience significantly lower rates of admission (0.3%).

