The third component of the package includes scheduled follow-up phone calls (days 1, 3, and 7 after referral to the HF clinic and every week after that) for 3 months [21]. The research nurse will give participants a list of call dates and will call each subject in the evenings between 6 pm and 9 pm. Each follow-up phone call will last 5-15 minutes [21] and is designed to review the content of the instructional session, encourage participants to continue weight and SOB self-monitoring, and record them in the daily diaries. Also, the research nurse will ask the participants about the color zone during the previous week and will recommend the appropriate action (see Figure 3). Also, we predict that during the call follow-ups, participants in the intervention group will report another symptom that may be due to a side effect of the medications or the disease. The research nurse will be able to provide the appropriate recommendation for each symptom reported in the intervention group during these (see Figure 4).

At the end of the one-hour instructional session in the HF clinic, a plastic folder containing the instructional booklet, weight, and SOB colored diaries, pen, pencil, eraser, and a pencil sharpener will be delivered to each subject in the intervention group. They will be asked to keep diaries clean and deliver them to the research nurse at the end of the study.

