#### Secondary Analysis

Independent *t* tests between 2 groups will compare the mean of the HF knowledge score before and at the end of the study. The HFQOL at baseline and at monthly time intervals will be compared by the *P* value correction based on the multiple comparisons.

In order to describe the surveillance, the median of admissions to health care settings will be used. Also, the Kaplan-Meier survival analysis will be applied for a descriptive comparison of the surveillance and, a log-rank test will be used to detect the significance difference between the 2 groups. A hazard ratio will be reported with 95% CI.

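### Hospital records are checked only after a patient reports an admission, and the planned median of admissions carries no information at the rates the protocol cites

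*Protocol article*

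**What the plan says.** The All-Cause Hospitalization section has the data collected from participants in both groups "by an outcome assessor blinded to study group assignment during monthly call follow-ups", each call covering the previous month. Two routes follow:

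- Outside THC: "In the case of admission to other health care settings except for THC, data will be collected according to the participants’ self-reporting".
- At THC, the recruiting hospital: "If the participant is admitted to THC, data will be confirmed by the hospital information system following participant self-reporting".

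No record search that starts from the list of randomised patients is described.

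On analysis, the Secondary Analysis section says that "the median of admissions to health care settings will be used". It adds that "the Kaplan-Meier survival analysis will be applied for a descriptive comparison of the surveillance" and that "a log-rank test will be used to detect the significance difference between the 2 groups", with a hazard ratio and 95% CI. Table 1 lists the outcome as a yes/no variable, but the analysis section names neither a count nor a proportion of patients admitted.

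The Introduction gives two admission rates. One is from a European registry, where "the rate of all-cause mortality and hospitalization at one-year follow-up was 8.1% and 28.2%, respectively". The other is 0.3% for Iranian patients, with no period stated. The Primary Outcome section cites low reported admissions in Iran as the reason hospitalization was not made primary.

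**The concern.** There are two separate weaknesses, one in how events are found and one in how they are summarised.

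**Finding events.** The hospital information system is consulted only once the patient has reported an admission. Used this way it can remove a false report or correct a date, but it cannot add an event. A THC admission has no stated route into the data if the patient forgets it, or if it falls in a month whose call was missed. When an arm is expected to yield only a few admitted patients, losing even one matters.

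**Summarising events.** A median count is 0 whenever more than half of the patients have no admission. At the rates the protocol cites, nearly all patients will have none. The descriptive statistic would then read 0 versus 0 whether or not the package changes admissions.

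**Working it through.** **Inputs.** 34 patients per arm and 68 in total (Sample Size); 3 months of follow-up; 28.2% hospitalized at one year in the European registry, and 0.3% in Iran (Introduction). Two assumptions are mine: a constant hazard within the year, and a one-year period for the 0.3%.

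**The plan's own figure.** The protocol states no event count, rate or power for hospitalization. Its only figure is the 68, which comes from the self-care outcome. With f = 0.168, three measurements and correlation 0.5, a repeated-measures within-between interaction calculation needs 60 patients. Then 60/0.9 = 66.7, so 67, or 68 as an even number. The 68 is taken as given here.

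**Step 1: expected patients admitted.** Three-month risk = 1 − (1 − annual risk)^(1/4).

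- At 28.2%: 1 − 0.718^0.25 = 0.0795. Per arm 34 × 0.0795 = 2.7; in total 68 × 0.0795 = 5.4.
- At 0.3%: 1 − 0.997^0.25 = 0.0008, which is about 0.05 patients in the whole trial.

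At the higher rate, one missed patient is 1/2.7 = 37% of an arm's expected events.

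**Step 2: chance that an arm's median exceeds 0.** With 34 patients the median is the mean of the 17th and 18th ordered values, so at least 17 patients must be admitted. P(X ≥ 17), X ~ Binomial(34, p):

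| Three-month risk p | P(arm median > 0) | P(both medians 0) |
|---|---|---|
| 0.0795 (28.2% per year) | about 1e-10 | above 0.9999 |
| 0.282 (whole annual risk within 3 months) | 0.006 | 0.988 |
| 0.30 | 0.011 | 0.977 |
| 0.40 | 0.155 | 0.714 |

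A three-month risk of 50% would correspond to 1 − 0.5^4 = 94% per year. If a median time to admission is meant, the Kaplan-Meier curve would have to fall to one half, and at the cited rates that median is not reached.

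**Step 3: what the time-to-event analysis would rest on.** Take a control risk of 0.0795 and a hazard ratio of 0.5. The intervention risk is 1 − (1 − 0.0795)^0.5 = 0.0405, so events = 34 × (0.0795 + 0.0405) = 4.1. By Schoenfeld's formula the two-sided 5% log-rank power is about 10%; 80% power needs 66 events. With 5 events, the 95% limits for the hazard ratio lie a factor of exp(1.96 × 2/√5) = 5.8 either side of the estimate. If the full 28.2% fell within 3 months, there would be about 15 events and 27% power.

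**Step 4: missed events.** The documents give no sensitivity for self-report, so this can only be illustrated. An assumed sensitivity of 70% to 90%, equal in both arms, loses 5.4 × 0.3 = 1.6 down to 5.4 × 0.1 = 0.5 events. Assumed sensitivities of 0.95 and 0.75 in the two arms would give an apparent risk ratio of 0.95/0.75 = 1.27 when there is no effect.

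**The case against.** The strongest reply has four parts.

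- **The median is not the whole analysis.** A reader might infer that a median of 0 leaves the outcome unable to show anything. The documents do not support that. The same section plans Kaplan-Meier, a log-rank test and a hazard ratio, which use dated first admissions and do not collapse when the median is 0. Their limit is the number of events. This part of the reply stands.
- **Reporting may well be equal.** The intervention arm has calls on "days 1, 3, and 7 after referral to the HF clinic and every week after that". Through day 84 that is 3 + 11 = 14, against 3 monthly calls for controls, and a reader might infer that reporting must differ by arm. But the nurse calls deliver the intervention, and recording admissions is not among their stated purposes. Admissions are collected by a blinded assessor at monthly calls in both arms. Better recall from weekly contact is possible, not demonstrated. This stands too.
- **Some missed admissions will surface later.** A patient still in hospital at the month 1 or month 2 call can report that stay at the next one. This narrows the gap. It does not cover a forgotten admission, a stay wholly inside a month whose call was missed, or one around the last call.
- **A descriptive summary can be left to the analysis plan.** That would answer silence, but here the article names the statistic, and it is one that its own cited rates make uninformative.

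**Conclusion.** The point holds in limited form. As written, the THC check confirms reported admissions and cannot find unreported ones; admissions elsewhere are not verified at all. The number and direction of missed events cannot be computed, so a reader who concludes that under-reporting would reverse the result goes further than the documents allow. What can be said is that about 2.7 events per arm, or far fewer at the Iranian rate, leave little room for loss.

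The median of admissions is practically certain to be 0 in both arms at either cited rate. This is an inference from those rates under a constant hazard, not a documented fact. It survives putting the whole annual risk into 3 months (98.8%) and weakens only as the three-month risk nears 40% to 50%. The log-rank test and hazard ratio remain valid to report, but on about 5 events or fewer a non-significant result would say almost nothing.

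This concerns a secondary outcome and is a low-cost improvement. It does not threaten the primary comparison.

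**What to change.** 1. Have the blinded assessor search the THC information system for every randomised patient over that patient's own 3 months, whether or not an admission was reported, and including patients not reached at a call or removed during follow-up.
2. Replace the median with the number and proportion of patients admitted and the admissions per patient-month by arm, with exact 95% CIs. The proportion should lead, because it matches the yes/no outcome in Table 1 and is not swayed by repeat admissions in one patient.
3. Keep Kaplan-Meier, the log-rank test and the hazard ratio with its 95% CI, and state that they are interpreted as descriptive.

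The cost is one search for 68 patients, in a system the trial already uses and by existing staff, plus revised wording. The search can still be done after follow-up ends. Admissions outside THC remain self-reported, and the report should say so.

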### Data Collection

Eligible patients will be asked to read and sign a written informed consent form. The research nurse will then collect demographic and clinical characteristics by participant self-reporting and from a medical chart and then record these in data collection forms (see Table 1). Also, participants will be asked to complete baseline surveys (SCHFI, HF knowledge, HFQOL, and health literacy) by themselves in the HF clinic before randomization.

In order to assess participant health literacy, we will use the Heart Failure-Specific Health Literacy Scale with Cronbach alpha=.71. It consists of 12 items each with 4 possible scores (1 to 4): inapplicable (1) to strongly applicable (4) where a higher score indicates a higher level of health literacy except items 1 to 4 [55]. The Iranian version of this scale was prepared after getting the developer’s permission. Thus, it was first translated into Persian by a forward-backward translation method. Then, face and content validity were approved by an expert’s opinion (nursing faculty, nurse practitioners, and cardiologists) and discussion with patients with HF. A pilot study was conducted to assess the reliability with 30 HF patients and where a Cronbach alpha value of .77 was determined. Deletion of items could not improve the value similar to the original scale. Therefore, we decided to retain all items [55]. We will ask the participants to complete the health literacy scale as a baseline survey.

In order to measure the HF knowledge at the end of the study, monthly self-care behavior, and the HFQOL, the outcome assessor will be blinded to study group assignments. The assessor will send the DHFKS, SCHFI, and MLHFQ to the participants in both groups by telegram mobile application in the morning of each monthly call follow-up and ask them to send answers before 6 pm of the same day.

### Participant Timeline

The SPIRIT 2013 template was used to schedule enrolment, interventions, and assessments (Table 1) [34]. A schematic representation of the study design is shown in Figure 5.

**Table 1 table1:** Time schedule for enrolment, interventions, and assessments in this study.

Time point			Staff member	Study period						
				Enrollment: *-t*_*1* _^a^	Allocation: 0	Post-allocation				Close-out: *t_x_*^b^
						*t_1_* ^c^	*f* _1_	*f* _2_	*f* _3_ ^d^	
**Enrollment**										
	Eligibility screen		Research nurse and HF^e^ specialist	✓	—^f^	—	—	—	—	—
	Informed consent		Research nurse and HF specialist	✓	—	—	—	—	—	—
	Baseline characteristics and surveys		Research nurse	✓	—	—	—	—	—	—
Allocation			Research nurse	—	✓	—	—	—	—	—
**Intervention**										
	Integrated package plus usual care		Research nurse	—	—	✓	✓	✓	✓	—
**Control**										
	Usual care		—	—	—	✓	✓	✓	✓	—
**Assessments (demographic/clinical)**										
	Age (years)		Research nurse	✓	—	—	—	—	—	—
	Gender (male/female)		Research nurse	✓	—	—	—	—	—	—
	Ethnicity		Research nurse	✓	—	—	—	—	—	—
	Marital status (married/single)		Research nurse	✓	—	—	—	—	—	—
	Income		Research nurse	✓	—	—	—	—	—	—
	**Level of education**									
		Elementary	Research nurse	✓	—	—	—	—	—	—
		High school	Research nurse	✓	—	—	—	—	—	—
		Academic	Research nurse	✓	—	—	—	—	—	—
	HF-Specific Health Literacy Scale		Research nurse	✓	—	—	—	—	—	—
	Body mass index (kg/m^2^)		Research nurse	✓	—	—	—	—	—	—
	Job (yes/no)		Research nurse	✓	—	—	—	—	—	—
	Insurance (yes/no)		Research nurse	✓	—	—	—	—	—	—
	Time with HF		Research nurse	✓	—	—	—	—	—	—
	**HF etiology (yes/no)**									
		Ischemic heart disease	Research nurse	✓	—	—	—	—	—	—
		Cardiomyopathy	Research nurse	✓	—	—	—	—	—	—
		Hypertension	Research nurse	✓	—	—	—	—	—	—
		Heart valve disease	Research nurse	✓	—	—	—	—	—	—
	NYHA^g^ functional class (II–IV)		Research nurse	✓	—	—	—	—	—	—
	Previous hospitalization (yes/no)		Research nurse	✓	—	—	—	—	—	—
	Hospitalization last 3 months? (yes/no)		Research nurse	✓	—	—	—	—	—	—
	Charlson comorbidity index		Research nurse	✓	—	—	—	—	—	—
	Ejection fraction (%)		Research nurse	✓	—	—	—	—	—	—
	Systolic blood pressure (mm Hg)		Research nurse	✓	—	—	—	—	—	—
	Diastolic blood pressure (mm Hg)		Research nurse	✓	—	—	—	—	—	—
	Heart rate (bpm)		Research nurse	✓	—	—	—	—	—	—
	Daily weight measure (yes/no)		Research nurse	✓	—	—	—	—	—	—
	**Medications (yes/no)**									
		Angiotensin-converting enzyme inhibitor	Research nurse	✓	—	—	—	—	—	—
		Angiotensin receptor blocker	Research nurse	✓	—	—	—	—	—	—
		Diuretics	Research nurse	✓	—	—	—	—	—	—
		Aspirin	Research nurse	✓	—	—	—	—	—	—
		Statins	Research nurse	✓	—	—	—	—	—	—
		Vitamin k antagonists	Research nurse	✓	—	—	—	—	—	—
		Allopurinol	Research nurse	✓	—	—	—	—	—	—
		Beta blocker	Research nurse	✓	—	—	—	—	—	—
		Digitals	Research nurse	✓	—	—	—	—	—	—
	Implantable cardiac devices (yes/no)		Research nurse	✓	—	—	—	—	—	—
	Prior cardiac surgery? (yes/no)		Research nurse	✓	—	—	—	—	—	—
	Arrhythmia in electrocardiography? (yes/no)		Research nurse	✓	—	—	—	—	—	—
	**Laboratory parameters (serum)**									
		Sodium	Research nurse	✓	—	—	—	—	—	—
		Potassium	Research nurse	✓	—	—	—	—	—	—
		Urea	Research nurse	✓	—	—	—	—	—	—
		Creatinine	Research nurse	✓	—	—	—	—	—	—
		Uric acid	Research nurse	✓	—	—	—	—	—	—
		Hemoglobin	Research nurse	✓	—	—	—	—	—	—
		Hematocrit	Research nurse	✓	—	—	—	—	—	—
		Fasting blood glucose levels	Research nurse	✓	—	—	—	—	—	—
